### Study Population

All pediatric patients (aged 18 years and younger) having scheduled surgery at the BRHC to repair a congenital heart defect using CPB, represent the target study population and will be screened for eligibility. Patients will be excluded from the study if either: (1) they require deep hypothermic circulatory arrest, (2) they are admitted for an emergency operation (patients with hemodynamic instability who require immediate surgical intervention), or (3) they and/or their next-of-kin do not provide written informed consent. We will also record specific reasons where surgeons are unwilling for the patient to be approached for the study. All reasons for ineligibility will be recorded on the study screening log.

We will aim to approach all next-of-kin (usually parents) and/or patients at preoperative clinics or on admission the day before surgery. Eligible next-of-kin and/or patients will be given a patient information leaflet (PIL), have the study explained to them, and will be given the opportunity to ask questions about the study. They will be given a minimum of 24 hours to consider the study prior to being asked to provide written informed consent if they are willing to participate in the study.

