### Randomization

Participants will be randomly assigned in a 1:1 ratio to either the hypothermic group or the normothermic group. Randomization will be stratified by age: 1 month or younger, 1 to 12 months, and older than 12 months. Allocations will be generated by computer using block randomization with varying block sizes. The allocation sequence will be prepared in advance of the study by a statistician independent of the study team. If a participant’s surgery is unexpectedly rescheduled, he/she will retain his/her study numbers and randomized allocation. Access to the allocation will be via a password-controlled secure database. Randomization will take place as close to the start of surgery as possible.

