#### Primary Outcomes

The co-primary endpoints are (1) duration of inotropic support, (2) intubation time, and (3) postoperative hospital stay (from date of surgery to discharge from cardiac ward). These data will be collected from medical notes and hospital charts.

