#### Secondary outcomes

Data will be collected to characterize the following secondary outcomes:

In-hospital mortality and morbidity rates will be recorded.Blood loss and transfusion requirements will be recorded.Preoperative and postoperative echocardiographic (ECG) findings will be recorded.Routine blood gas and blood test results will be recorded.Renal function will be measured by testing urinary albumin, urinary creatinine, retinal binding protein (RBP), N-acetyl-β-glucosaminidase (NAG), and neutrophil gelatinase-associated lipocalin (NGAL) [28-33]. All markers of renal damage will be measured preoperatively and at several time-points postoperatively.Cerebral function will be measured by testing for glial fibrillary acidic protein (GFAP), a serum marker of traumatic brain injury [34,35]. GFAP levels will be measured preoperatively and at several time-points mid- and postoperatively.Regional oxygen saturation of blood in the cerebral cortex will be measured at approximately 15-minute intervals during the operative period using near-infrared spectroscopy (NIRS).Neuropsychological development will be assessed using the NEPSY-II psychometric tool [36]. Neuropsychological assessments will be performed on patients aged between 3-16 years old, preoperatively and at 3 and 12 months postoperatively. These tests are intended as a tool to allow the assessment of both basic and complex aspects of cognition across the following 6 functional domains: attention and executive functions, language, memory and learning, sensorimotor functions, social perception, and visual-spatial processing.Cardiac tissue biopsies from heart tissue discarded during the surgical procedure and considered clinical waste will be analyzed for biochemical markers and RNA analysis on a subset of 32 patients. If available, 4 samples will be collected from each patient in this subset; 2 samples will be collected immediately after institution of CPB and a further 2 samples will be collected 10-15 minutes after reperfusion. Biochemical tests will be performed on the biopsies to determine the presence of a range of important proteins and metabolites, and transcriptional profiling by RNA extraction will be performed with the aim to help establish whether any genomic expression changes associated with hypothermia could be prevented by using normothermic techniques.

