### Statistical Analyses

#### Plan of Analysis

Binary outcomes will be compared using logistic regression. Quantitative outcomes will be transformed if necessary to achieve approximately normal distributions and compared using linear regression and time to event variables will be analyzed using survival methods. Outcomes with repeated measures (longitudinal data) will be analyzed using mixed models, which allow for unbalanced data. Alternative correlation structures will be considered, and the sensitivity of the results to the choice of structure examined. Analyses will be adjusted for age group (stratification factor). All analyses will be carried out on the basis of intention-to-treat. Outcomes will be reported as effect sizes with 95% confidence intervals.

Specific morbidities are too infrequent for the study to be able to detect statistically significant differences between groups. Frequencies of these adverse outcomes will be tabulated, in line with guidelines for reporting adverse events in trials, and reported in accordance with International Conference on Harmonisation Good Clinical Practice guidelines.

The analysis of the microarray data for the gene expression study—including normalization, noise reduction, and analysis using, for example, unsupervised hierarchical clustering and relevance network analysis—will be performed using Genespring 7 software. Following determination of the gene expression profiles, bioinformatics data mining tools (Genespring 7) will be used to identify the gene expression profiles that are differentially significant and to cluster them by biological function. This is vital for generating hypotheses about their role. Predefined stringent criteria will be used to select candidate genes for validation; only genes with statistically significant differential expression will be considered. Patterns of change in signaling pathway networks will be explored.

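### Age is adjusted for only through three randomisation bands: the factor is constant in the NEPSY-II models and leaves age differences beyond 12 months unadjusted in the co-primary models, at a modest cost in precision

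*Protocol article*

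**What the plan says.** All references are to the protocol article.

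- **Plan of Analysis:** "Analyses will be adjusted for age group (stratification factor". No other adjustment covariate is named. The Subgroup Analyses section adds only interaction terms for study phase.
- **Randomization:** "Randomization will be stratified by age: 1 month or younger, 1 to 12 months, and older than 12 months". The bands are not split further.
- **Study Population:** "All pediatric patients (aged 18 years and younger) having scheduled surgery" form the target population, so the oldest band runs from just over 1 year to 18 years.
- **Secondary outcomes:** "Neuropsychological assessments will be performed on patients aged between 3-16 years old, preoperatively and at 3 and 12 months postoperatively".
- **Primary Outcomes:** "The co-primary endpoints are (1) duration of inotropic support, (2) intubation time, and (3) postoperative hospital stay".

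**The concern.** The adjustment sentence covers every analysis, but how much it achieves depends on where the children fall in the bands. For NEPSY-II they all fall in one. Two tested children can differ in age by up to 13 years (16 − 3) and still have the same covariate value. In the co-primary models the bands separate neonates, infants and older children, yet a toddler and a 17-year-old count as the same age. The three durations have no pre-operative value that could stand in for age.

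If age within the oldest band is related to outcome, two things follow. Variance that a recorded covariate could remove stays in the residual. A chance difference in age between the arms within that band also goes uncorrected, because neither the stratification nor the model addresses it.

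**Working it through.** **1. Is the factor constant for NEPSY-II?** The tested range of 3 to 16 years lies wholly above 12 months. For these children the age-group indicators are collinear with the intercept (the design matrix for intercept plus age group has rank 1). The stated adjustment therefore removes none of the age variation. This follows from the bands alone.

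**2. How wide is the oldest band?** It covers 17 of the 18 eligible years, or 94%. That is a share of calendar years. The article does not give the share of children over 12 months.

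**3. Chance age imbalance in NEPSY-II.** The number tested is not given. Assume ages uniform on 3 to 16 (SD = 13/√12 = 3.75 years) and n children per arm. The standard error of the difference in mean age between arms is 3.75 × √(2/n):

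| n per arm (assumed) | SE of difference (years) |
|---|---|
| 10 | 1.7 |
| 20 | 1.2 |
| 30 | 1.0 |

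**4. Possible precision gain in NEPSY-II.** If age explains a share R² of variance beyond the other covariates, the standard error is multiplied by √(1 − R²). For assumed R² of 5%, 10%, 20% and 30%, it falls by 2.5%, 5%, 11% and 16%. The share is near zero if scores are age-standardised or the baseline score absorbs age.

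**5. Length of stay: the plan's own figure.** The Sample Size section gives a geometric mean of 6.2 days, log-scale SD 0.4, a 1-day reduction, 100 per group, two-sided 5% and 90% power.

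- Difference: ln(6.2/5.2) = 0.1759.
- Standard error: 0.4 × √(2/100) = 0.0566.
- Ratio: 0.1759/0.0566 = 3.109.
- Power: Φ(3.109 − 1.960) = 87.5%. For 90% power, 109 per group would be needed.

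This does not quite reproduce 90%. An unrounded SD of about 0.383 gives exactly 100 per group, so the gap is consistent with rounding and is separate from the present point.

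**6. Length of stay: what continuous age could add.** The article gives no age effect, so R² is assumed. A simulation used 200 children, 55% of them in the oldest band (assumed), age acting only within that band, and age group in both models:

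| R² of age within oldest band (assumed) | Power, age group only | Power, plus continuous age | Gain (points) |
|---|---|---|---|
| 5% | 88.2% | 89.0% | 0.9 |
| 10% | 85.6% | 87.7% | 2.1 |
| 20% | 87.4% | 90.7% | 3.4 |

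The age-group-only column should be constant; its spread is simulation error (3,000 runs per row). Type I error stayed near 5% in both models.

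A direct calculation agrees. The pooled residual variance falls by 0.55 × R², that is 2.75%, 5.5% and 11%. The ratio becomes 3.109/√(1 − 0.55 R²) = 3.153, 3.199 and 3.296, and power 88.4%, 89.2% and 90.9%. Against 87.5%, the gains are 0.9, 1.7 and 3.4 points.

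**The case against.** The strongest case on the other side is that the plan contains no error. Adjusting for the stratification factor is a valid analysis under stratified randomisation, and the form of a further covariate is often left to the analysis plan. The first part stands in full. The second stands only in part, because the article does not stay silent: it names the covariate and identifies it with the three bands.

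A reader might infer more than the article supports, in four ways.

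- **Bias or inflated type I error.** Allocation is random within bands, so the comparison is unbiased, and the simulation showed error near 5% with or without continuous age.
- **A rise in power from 87% to 89%, 91% or 94%.** These figures come from letting age remove 5%, 10% or 20% of the whole variance of 0.4². The article does not say that the SD of 0.4 is net of age group, so this gives the planned bands no credit. About 8% of variance explained would bring power to 90% (1 − (3.109/3.2415)² = 0.08), and the bands might supply that already.
- **Most children unadjusted.** Seventeen of 18 years is not a share of patients. The Background stresses early repair, and no age distribution is given.
- **A known loss in NEPSY-II.** A pre-operative assessment is scheduled and repeated measures go into mixed models. The article does not say how scores are scaled or how baseline enters, so the loss cannot be established.

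It is also fair to object that continuous age should not be added to every analysis. Specific morbidities are described as too infrequent to compare, the biopsy subset has 32 patients, and extra terms are not free there. In logistic or hazard models a prognostic covariate also changes the conditional effect being estimated, so the variance formula above does not carry over. This limits the fix.

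**Conclusion.** The point holds as a modest improvement in precision and in protection against chance imbalance. Two parts are certain from the text: the stated age adjustment is empty in the NEPSY-II models, and it cannot distinguish children over 12 months from one another in the co-primary models. The validity of the planned analysis is not in question.

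The size is not known. On length of stay it is about 1 to 3 points of power, assuming 55% of children in the oldest band, age explaining 5% to 20% of variance within it, and a linear model on the log scale. In NEPSY-II it ranges from near zero (age-standardised scores, or baseline absorbing age) to a 16% smaller standard error if age explained a further 30% of variance. The NEPSY-II part is the clearer of the two, but it concerns one secondary outcome in a subset of unstated size.

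**What to change.** In the Plan of Analysis, limit the change to the models where it can help:

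- **Co-primary outcomes and other continuous outcomes with adequate numbers:** keep the randomisation age group and add age at surgery as a continuous covariate, with its form (for example log age) fixed before outcomes are compared by arm.
- **NEPSY-II models:** use age in years in place of the constant age group, unless age-standardised scores are analysed. State which scores are used.
- **Sparse binary outcomes and the 32-patient biopsy subset:** leave as planned.

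If a co-primary duration is analysed by survival methods, state that the reported effect is conditional on age.

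The cost is a short change to the text and 1 to 2 degrees of freedom per model. One check is needed first. The pooled analysis of 200 includes 59 children from Thermic-1, and the article does not say how their age was recorded, so the sponsor should confirm that exact age is available for them. No new patients or procedures are required.

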### Sample Size

#### Primary Outcomes

The geometric mean postoperative hospital stay in our institution is estimated to be 6.2 days, with standard deviation (on the logarithmic scale) of 0.4. A sample size of 100 participants per group would be sufficient to allow us to detect a clinically relevant 1 day or greater reduction in mean length of stay with 90% power, assuming a 5% level of statistical significance (2-tailed).

Using estimates for ventilation time and duration of inotropic support from our institution, a total sample size of 200 would also be sufficient to detect a 16% reduction in ventilation time (3 hours), and a 13% reduction in inotropic support (4.7 hours). All these differences represent clinically relevant reductions.

In an earlier RCT comparing the same 2 interventions carried out at our institution (Thermic-1), 59 participants were recruited. The primary outcomes for this earlier study were biochemical markers of organ injury, but clinical outcome data were also collected. For the current study (Thermic-2), 141 participants have been recruited. The clinical data from the 2 studies will be combined for assessment of the clinical outcomes, giving a total sample size of 200 participants for analysis.

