#### Secondary Outcomes

This sample size will also be able to detect clinically relevant differences in secondary outcomes with 90% power. For full details, see Multimedia Appendix 1.

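### Specific morbidities are to be tabulated without a between-arm estimate because they are too rare to reach significance; low power is a reason not to test them, not a reason to leave out the interval

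*Protocol article*

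**What the plan says.** The Secondary outcomes section of the protocol article lists death and complications in hospital together: "In-hospital mortality and morbidity rates will be recorded".

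The Plan of Analysis then sets two general rules. The method is "Binary outcomes will be compared using logistic regression", with adjustment for age group. The reporting rule is "Outcomes will be reported as effect sizes with 95% confidence intervals".

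The next paragraph treats individual morbidities differently. It gives the reason, "Specific morbidities are too infrequent for the study to be able to detect statistically significant differences between groups", and then the handling: "Frequencies of these adverse outcomes will be tabulated, in line with guidelines for reporting adverse events in trials". It mentions no between-arm estimate or interval for these events. It does not name mortality or an overall morbidity rate.

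**The concern.** The only reason offered for the different handling is that significance is out of reach. That is a sound reason not to run a separate test on each rare event. It does not bear on estimation. When events are few, the interval is the part of the report that shows what the trial could not exclude, so it is most useful where the test is least useful.

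Followed as written, the plan gives readers two columns of counts and a remark that differences could not be detected. Similar counts are easily taken as similar safety. The risk is greater because the sample size section says of the same trial: "This sample size will also be able to detect clinically relevant differences in secondary outcomes with 90% power". It names no exception for morbidity in the article itself, although its details are in an appendix that is not shown. The comparison is about organ protection in children, and either temperature could carry harm, so the size of the remaining uncertainty should be on the page.

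**Working it through.** **The plan's own figure.** No figure is stated for morbidity. The only fully specified calculation is for hospital stay: "A sample size of 100 participants per group would be sufficient to allow us to detect a clinically relevant 1 day or greater reduction", with 90% power, two-sided 5%, and a geometric mean "estimated to be 6.2 days, with standard deviation (on the logarithmic scale) of 0.4".

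- Effect on the log scale: ln(6.2/5.2) = 0.176.
- n per group = 2 × 0.4² × (1.960 + 1.282)² / 0.176² ≈ 109. With 100 per group, power is 87.5%.
- The reduction detectable with 100 per group at 90% power is 16.8%, or 1.04 days, so rounding explains the gap.

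This has no bearing on the present point beyond fixing the arm size of 100 (59 participants from Thermic-1 plus 141 from Thermic-2, 200 in all).

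**Is the low-power premise right?** The event rates are assumptions. For risks p1 and p2 with mean p̄ and n = 100 per arm:

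power = Φ{(|p2 − p1| − 1.96·SE0) / SE1}, where SE0 = √(2p̄(1 − p̄)/n) and SE1 = √((p1(1 − p1) + p2(1 − p2))/n).

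Example, 5% to 10%: SE0 = 0.0373 and SE1 = 0.0371, so power = Φ((0.05 − 0.0730)/0.0371) = Φ(−0.62) = 27%.

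| Assumed risk, doubled | Power |
|---|---|
| 1% to 2% | 8% |
| 2% to 4% | 13% |
| 5% to 10% | 27% |
| 10% to 20% | 51% |
| 20% to 40% | 88% |

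The premise is right for uncommon events.

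**What would an interval show?** Newcombe's score interval combines the Wilson limits (l, u) of each arm. When the two counts are equal, the limits for the difference are ±√((p − l)² + (u − p)²).

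- 0 v 0 of 100: l = 0 and u = 3.84/(100 + 3.84) = 3.7%, giving ±3.7 points.
- 10 v 10 of 100: l = 5.5% and u = 17.4%, giving ±√(4.5² + 7.4²) ≈ ±8.7 points.

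| Events per arm, of 100 | 95% limits for the risk difference (points) |
|---|---|
| 0 v 0 | ±3.7 |
| 1 v 1 | ±4.5 |
| 2 v 2 | ±5.2 |
| 5 v 5 | ±6.8 |
| 10 v 10 | ±8.7 |

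With about 70 per arm (Thermic-2 alone, 141/2), 0 v 0 gives ±5.2 and 7 v 7 gives ±10.5.

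An unequal example with 100 per arm is 6 v 2. The difference is 4.0 points and the interval runs from about −1.9 to +10.6. A table showing 6 and 2 does not tell the reader that an excess of ten points is still possible. The interval does.

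**The case against.** The strongest reply is that the plan is open and conventional. It says that rare events cannot be compared with adequate power, does not claim that there is no difference, and follows guidelines for reporting adverse events. Those guidelines are not to hand, so nothing here shows that they would rule intervals in or out. Tabulating rare events is common practice, and a full protocol or analysis plan could add detail. Much of this stands, and it keeps the point modest. It does not answer the point, because the article does more than leave detail open: it states a handling and a reason, and the reason does not support leaving out the estimate.

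A reader might also infer more than the text supports:

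- **That the whole mortality and morbidity outcome gets no comparison.** The exemption is worded for specific morbidities. Mortality and any overall morbidity rate remain binary outcomes under the logistic regression and confidence interval rules.
- **That harm cannot be bounded.** Anyone with counts and arm sizes can calculate a risk difference and its interval, as above. The plan does not commit to reporting them.
- **That organ injury goes without intervals.** Inotrope duration, intubation time, hospital stay, renal markers, GFAP, cerebral oxygen saturation and NEPSY-II all stay under the general reporting rule.
- **That a composite of any morbidity or death, or a sparse-data regression method, is missing.** The composite would be a new outcome, and the article lists no components for it. The regression method is detail that an analysis plan ordinarily supplies.

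**Conclusion.** The point holds for specific in-hospital morbidities only. The plan departs from its own estimate-and-interval rule for them, for a reason that justifies not testing but does not justify not estimating. It is a reporting fault with a cheap remedy. It does not affect the design, the primary outcomes or the handling of mortality.

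On size: with 100 per arm and equal counts of 0 to 10 events, differences of about 4 to 9 percentage points either way would remain compatible with the data, and the planned table would not say so. This rests on assumed counts, since the article gives no morbidity rates, and on the pooled total of 200 splitting evenly. With Thermic-2 alone the limits are wider.

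**What to change.** Keep the frequency table and the statement that individual morbidities will not be tested. Add for each specific morbidity:

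- the number of children with the event and the number in the arm;
- the risk difference, normothermic minus hypothermic, with a 95% score or exact interval;
- no p-value.

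State under the table that the intervals are descriptive and unadjusted, and that an interval including zero does not show equal safety. One sentence should confirm that mortality and any overall morbidity rate follow the general rule for binary outcomes.

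The cost is a change of wording and a few more table columns, with no new data. The downside is a table with many wide, unadjusted intervals, some of which may exclude zero by chance; the descriptive label is there for that reason.
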